## Abstract

The optimal mammography screening strategy for women aged 45–49 years is a matter of debate. We present the RIBBS study protocol, a quasi-experimental, prospective, population-based study comparing a risk- and breast density-stratified screening model (interventional cohort) with annual digital mammography (DM) screening (observational control cohort) in a real-world setting. The interventional cohort consists of 10,269 women aged 45 years enrolled between 2020 and 2021 from two provinces of the Veneto Region (northen Italy). At baseline, participants underwent two-view digital breast tomosynthesis (DBT) and completed the Tyrer-Cuzick risk prediction model. Volumetric breast density (VBD) was calculated from DBT and the lifetime risk (LTR) was estimated by including VBD among the risk factors. Based on VBD and LTR, women were classified into five subgroups with specific screening protocols for subsequent screening rounds: (1) LTR ≤ 17% and nondense breast: biennial DBT; (2) LTR ≤ 17% and dense breast: biennial DBT and ultrasound; (3) LTR 17–30% or LTR > 30% without family history of BC, and nondense breast: annual DBT; (4) LTR 17–30% or > 30% without family history of BC, and dense breast: annual DBT and ultrasound; and (5) LTR > 30% and family history of BC: annual DBT and breast MRI. The interventional cohort is still ongoing. An observational, nonequivalent control cohort of 43,000 women aged 45 years participating in an annual DM screening programme was recruited in three provinces of the neighbouring Emilia-Romagna Region. Cumulative incidence rates of advanced BC at three, five, and ten years between the two cohorts will be compared, adjusting for the incidence difference at baseline.

*Trial registration* This study is registered on Clinicaltrials.gov (NCT05675085).

## Background

The 2006 European guidelines for mammography screening endorsed organized screening programmes to target women aged 50–69 years [1], a recommendation supported by leading medical agencies [2]. As a result, only a limited number of European countries and regions have adopted organized screening for women aged 40–49 or 45–49 years, usually with a two-year screening interval [3].

In 2017, the European Commission’s Breast Cancer Guidelines Development Group conditionally recommended mammography screening for women aged 45–49 years [4]. However, the optimal screening interval remained undecided, with proposals for biennial or triennial rather than annual screening. The evolving diagnostic landscape has underscored the need to determine the most effective screening frequency.

Exploration of screening intervals for younger women is intertwined with risk-stratified screening, which tailors screening decisions to an individual’s breast cancer risk by considering age at onset, screening frequency, and imaging modality [5]. Breast cancer research has highlighted the different aspects of the disease, which include genotypes, phenotypes, prognosis and therapeutic responses. This shift toward personalized treatment of breast cancer reflects the broader trend of precision medicine, which tailors therapy to individual characteristics [6–8].

Similarly, the traditional “one-size-fits-all” approach to breast cancer screening, which is based solely on the age criterion, has become obsolete because it does not take account of the biologic and epidemiologic complexity of the disease [9, 10]. Breast cancer is the result of a complex web of causation involving multiple interacting risk factors. This has given rise to a debate about risk-based screening protocols [11–16] and to the development of many risk models that incorporate classic risk factors, such as the patient age, family history of breast and ovarian cancer, personal history and reproductive history [17–20]. Over the years, breast density [21] has been incorporated into some risk models [22–24] in order to improve the accuracy of risk prediction. In fact, breast density can mask tumours and increase the interval cancer rates [25], which has suggested the use of supplemental imaging for women with dense breasts in screening programmes [26–28]. In addition, breast density is independent of other risk factors and is associated with increased risk that is not explained by its masking effect [21].

Although the potential benefits of screening stratified by density and risk are promising, two critical key challenges require attention. First, there are significant gaps in our knowledge base, especially regarding the relative effectiveness of different stratified protocols compared with each other and with traditional mammography screening [20, 29, 30]. To answer these scientific questions, a number of randomized controlled trials are underway [16, 31], as well as mathematical modeling studies measuring the effectiveness and cost-effectiveness of different screening frequencies [32–34].

Second, the implementation of screening programmes stratified by breast density and risk faces organizational and resource barriers. These include training, performance, workload, and financial sustainability within the existing healthcare system [35, 36]. Consequently, further observational studies of screening practices stratified by breast density and risk are essential [30].

This article introduces an innovative study protocol that offers a new perspective. Our study employs a quasi-experimental, prospective, population-based approach to evaluate the efficacy and feasibility of a screening model stratified by breast density and risk for women aged 45–49 years. Our goal is to evaluate the impact of this new screening approach in a real-world setting, contrasting it with a standard public health screening regimen. The quasi-experimental design provides an optimal framework for examining both the efficacy and feasibility of this innovative screening method.

## Materials and methods

### Context

In Italy, the public health system offers mammography screening every two years for women aged 50–69 years. Conversely, only a few regions, notably Emilia-Romagna, have implemented annual mammography screening for women aged 45–49 years [37, 38]. In contrast, the Veneto Region, like most Italian regions, does not yet have a mammography screening programme for women aged 45–49 years, despite the fact that breast cancer incidence rates are comparable to those observed among women aged 50–54 years [39, 40].

In 2018, the Veneto Institute of Oncology (IOV) addressed this gap by proposing a project to the Veneto Region, aiming to explore the feasibility and sustainability of a personalized screening programme. This innovative approach incorporates tomosynthesis, individual breast density, and risk estimation to personalize screening of women aged 45–49 years. The Regional Administration approved a feasibility study focusing on 45-year-old women residing in the provinces of Padua and Rovigo, totaling about 10,000 women per year. Given the limited pool of eligible participants, a quasi-experimental approach was adopted. In this setup, IOV formed the prospective cohort, while the observational control cohort was enrolled from the Emilia-Romagna Region.

### Study design

The study uses a quasi-experimental design of pre-post comparison with a non-equivalent control group [41]. Quasi-experimental designs, wich are used when random intervention assignment is impractical or unethical, reflect real-world conditions and allow for generalization. Despite practicality, cost-effectiveness, and higher external validity, this design may suffer from lower internal validity due to systematic differences between interventional and control groups. Nonetheless, non-experimental designs have been already used to assess the impact of public health mammography screening on the incidence of advanced breast cancer [42, 43].

We recruited a prospective interventional screening cohort of 45-year-old women from two provinces of the Veneto Region. These women, after initial screening, were divided into five subgroups based on their breast density and individual risk and were referred for different screening intervals and imaging protocols until the age of 49 years. At the same time, we assembled an observational cohort from the Emilia-Romagna Region, composed of women of the same age who underwent standard annual mammography screening. This population will serve as a nonequivalent control for comparative purposes.

The study hypothesis is that a screening model stratified by breast density and risk is more effective and sustainable in reducing the incidence of advanced breast cancer than standard annual mammography screening.

Both the interventional and control cohorts are studied using a two-phase design involving a pre-screening period followed by a screening period. The pre-screening phase measures the baseline incidence rate of breast cancer in women aged 45–49 years in both populations. This baseline assessment helps calculate the ratio of the incidence rate at baseline between the Veneto Region and the Emilia-Romagna Region for subsequent statistical adjustment. During the screening period, the two screening models are implemented, and cumulative incidence rates of advanced breast cancer are assessed over 3 years, 5 years and 10 years (at least). The ratio of the cumulative incidence rate in the interventional cohort to that found in the observational control cohort, adjusted for differences in incidence at baseline, is calculated. The decision to evaluate the results at three-year intervals stems from previous research that demonstrated a significant decline in the incidence of pT2-4 stage breast cancer from the third year of screening [44]. The extended follow-up duration takes into account the potential lasting preventive impact of screening beyond age 50 and incorporates the common biennial digital mammography screening procedure for women over age 50.

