### Outcome measures

The primary and secondary outcome measures are listed in Table 1. The primary measure of the effectiveness of screening stratified by breast density and risk, compared with conventional annual mammography, will be the cumulative incidence of advanced breast cancer. In particular, the focus will be on stage II or higher cancer throughout the follow-up period. Most of the secondary outcome measures are part of the core indicators used in the annual national survey of regional mammography screening programmes in Italy. These indicators were defined by the Italian Group for Mammography Screening and the Italian National Centre for Screening Monitoring [48]. They constitute the benchmark for reporting outcomes of breast cancer screening programmes in Italy.

**Table 1 Tab1:** Primary and secondary outcome measures in the RIBBS study

	Description
Primary outcome meausure: cumulative incidence of advanced breast cancer	Measure of effectiveness of screening stratified by breast density and risk compared with standard annual digital mammography. Focuses on stage II or higher cancer throughout the follow-up period
Secondary outcome measures	
Recall rate	Number of women recalled for further diagnostic evaluation per thousand women undergoing each of the two screening protocols
Cancer detection rate	Number of women with breast cancer detected by screening (topographic code C50 [47]) per thousand women undergoing each of the two screening protocols
Proportional incidence of interval cancer	Number of women diagnosed with interval cancer (detected after a negative screening episode) divided by the expected number of breast cancer cases in the absence of screening, by screening protocol and interval year
Total assessment rate	Number of women undergoing diagnostic evaluation per thousand women undergoing each of the two screening models, further subdivided into non-invasive and invasive assessment rates
Surgical referral rate	Number of women referred for excisional biopsy or definitive surgical treatment per thousand women undergoing each of the two screening protocols
Surgery rate	Number of women undergoing excisional biopsy or definitive surgical treatment per thousand women undergoing each of the two screening protocols
Benign lesion detection rate	Number of women with any histologically diagnosed benign lesion per thousand women undergoing each of the two screening protocols

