### Sample size

Sample size calculations focused specifically on the primary outcome measure of the personalized screening procedure. This primary outcome measure revolves around assessing the reduction in the incidence of advanced breast cancer in the interventional cohort compared with the observational control cohort.

Considering the real-world context of the study and the constraints associated with enrolling participants in both cohorts, the sample size calculations encountered some limitations. The enrollment of patients in both cohorts was limited by factors such as available space and tight timelines due to the initial approval period granted by the Veneto Region. This consequently prevented expansion of the cohorts beyond the approved period.

Given the impossibility of accurately determining the sample size required to detect a specific effect on the primary outcome with the desired statistical power, our approach involved estimating the minimum detectable reduction in the incidence of advanced BCs using the sample size provided and ensuring a minimum power of 80%. The sample sizes available to conduct a one-sided test comparing the null hypothesis H0: rate ratio ≥ 1.000 and the alternative Ha: rate ratio < 1.000, using the W5 Variance Stabilized test statistic, were determined in 43,000 subjects in the observational control cohort and 10,269 subjects in the total interventional screening cohort, both over a 5-year exposure period. With these designated sample sizes, the study is able to achieve a power of 80.5% in detecting an event rate ratio under the alternative hipothesis (RRa) of 0.810. The event rate in the observational control cohort (λ1) is estimated to be 0.004017, based on the incidence rate of BC at baseline. Specifically, the significance level (alpha) used in the test is 0.050.

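### The primary superiority outcome has no single decision horizon: it is compared at 3, 5 and 10 years, defined over all follow-up, and sized at 5 years only

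*Protocol article*

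**What the plan says.** Four parts of the protocol article bear on when the primary comparison is made.

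- **Abstract and Study design.** The Abstract states that "Cumulative incidence rates of advanced BC at three, five, and ten years between the two cohorts will be compared". Study design repeats the three horizons, saying that "cumulative incidence rates of advanced breast cancer are assessed over 3 years, 5 years and 10 years (at least"), and ranks none of them. Its rationale for the early evaluation, "The decision to evaluate the results at three-year intervals stems from previous research", does not describe a schedule of 3, 5 and 10 years.
- **Outcome measures, Table 1.** The primary outcome is cumulative incidence of advanced breast cancer, and the entry reads "Focuses on stage II or higher cancer throughout the follow-up period". It gives no time point.
- **Statistical analysis.** Follow-up is truncated at the 75th percentile of the available follow-up times. This rule is not linked to 3, 5 or 10 years. Results are incidence rate ratios with 95% confidence intervals, adjusted for pre-intervention incidence.
- **Sample size.** One calculation is given, a "one-sided test comparing the null hypothesis H0: rate ratio ≥ 1.000", for "43,000 subjects in the observational control cohort and 10,269 subjects in the total interventional screening cohort, both over a 5-year exposure period", and "the significance level (alpha) used in the test is 0.050".

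The Study design and Study hypothesis sections state a superiority hypothesis, also without a time point.

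**The concern.** There is one superiority hypothesis, one full 5% alpha, and more than one analysis that could be presented as its test. The four sections give four descriptions of the horizon, and only the Sample size section ties a horizon to an error rate and a power.

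The 3-year data mature before the 5-year data. Without a declared decision horizon, a favourable early result could be reported as the primary finding, and a later one could be used if the early one missed. The quoted 5% error and 80.5% power belong to a single test at 5 years. They do not describe a procedure in which any of three looks may succeed.

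**Working it through.** **Inputs (Sample size section).** Control women n1 = 43,000; interventional women n2 = 10,269; control rate λ1 = 0.004017; rate ratio RR = 0.810; one-sided alpha 0.05 (z = 1.645); exposure 5 years; stated power 80.5%. The horizons of 3, 5 and 10 years come from the Abstract and Study design.

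**Step 1: reproduce the stated power.** Expected events are E1 = n1·T·λ1 and E2 = n2·T·λ1·RR. At T = 5:

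- E1 = 43,000 × 5 × 0.004017 = 863.7
- E2 = 10,269 × 5 × 0.004017 × 0.81 = 167.1

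Log rate ratio: power = Φ(|ln RR| / √(1/E1 + 1/E2) − 1.645). Here |ln 0.81| = 0.2107 and √(1/863.7 + 1/167.1) = 0.0845. The ratio is 2.493, and Φ(2.493 − 1.645) = 80.2%.

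Variance-stabilised form, with ρ = n2/n1 = 0.2388: the mean of the statistic is 2[√(ρ(E1 + 3/8)) − √(E2 + 3/8)] / √(1 + ρ) = 2.560, and Φ(2.560 − 1.645) = 82.0%. A Poisson simulation gives 82.4%.

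Both formulas lie within 2 points of 80.5%, so the stated figure reproduces as a 5-year calculation with λ1 per woman-year. Read as a 5-year cumulative rate, λ1 would give only about 30%.

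**Step 2: power at the other two horizons, same inputs.**

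| T (years) | E1 | E2 | Power, log RR | Power, variance-stabilised |
|---|---|---|---|---|
| 3 | 518.2 | 100.2 | 61.3% | 62.8% |
| 5 | 863.7 | 167.1 | 80.2% | 82.0% |
| 10 | 1,727.3 | 334.1 | 97.0% | 97.7% |

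At 3 years the rate ratio detectable with 80% power is about 0.76, not 0.81. The 3-year row assumes that the full effect is present from the start of follow-up.

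**Step 3: type I error if a claim is open at any horizon.** With a constant event rate, information grows in proportion to time, and cumulative comparisons at ti < tj have correlation √(ti/tj):

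- 3 and 5 years: √(3/5) = 0.775
- 3 and 10 years: √(3/10) = 0.548
- 5 and 10 years: √(5/10) = 0.707

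From the trivariate normal distribution:

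- P(any z > 1.645) = 10.3%, against 5% for one test.
- P(any z > 1.960) = 5.5%, against 2.5%, if the criterion is a 95% interval lying wholly below 1.
- The 3- and 5-year looks alone at z > 1.645 give 7.7%.

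**Step 4: allow for the baseline adjustment.** The adjusted rate ratio uses one pre-intervention correction at all three horizons. If its uncertainty is carried into the interval, it is shared and raises the correlations. Let its variance be k times the 5-year log-IRR variance. The correlation for ti < tj becomes √[(5/tj + k)/(5/ti + k)]. The article gives no value for k, so the range below is an assumption.

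| k | Corr 3–5 | Corr 3–10 | Corr 5–10 | P(any z > 1.645) |
|---|---|---|---|---|
| 0 | 0.775 | 0.548 | 0.707 | 10.3% |
| 0.5 | 0.832 | 0.679 | 0.816 | 9.4% |
| 1 | 0.866 | 0.750 | 0.866 | 8.9% |
| 2 | 0.905 | 0.826 | 0.913 | 8.2% |

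**Step 5: the alternatives.** With 5 years as the only confirmatory look, error stays at 5% and power at 80 to 82%. If all three looks were confirmatory with a common boundary (k = 0), that boundary would be z = 2.003 (one-sided p < 0.0226). Power would then be about 49%, 71% and 95% at 3, 5 and 10 years, so the 5-year test would lose about 11 points (82.0% to 71.1%).

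**The case against.** The best defence is that 5 years is already the design horizon in substance. The Sample size section says that it addresses the primary outcome, and it sizes one test, "both over a 5-year exposure period". On this view only a label is missing, and the ranking of horizons may sit in an analysis plan that is not shown. A multiplicity procedure could indeed sit there. The time point of the primary outcome, however, goes with the outcome definition and the sample size. The article sets out both and gives them different horizons, so this is an inconsistency in its own text.

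The defence also notes that no section plans three 5% tests or allows a claim at the first crossing. The text speaks of comparing and assessing, and the analysis reports 95% intervals. Study design gives the early and the extended evaluation different purposes. This stands. A reader might infer that the plan doubles its false-positive rate, but the article states no success rule at all. The inflation is conditional on a claim being open at every horizon, and 10.3% is the upper case in Step 4.

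Two further inferences should be resisted:

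- **Bias at 3 years.** A reader might infer that a 3-year cut favours women on the biennial schedule, whose next screen falls after it. The net direction cannot be settled from the article. Follow-up starts at the first screen, so cancers found there count, and the Study hypothesis section expects more sensitive imaging in the interventional cohort. A longer gap may also let tumours reach stage II before year 3. The share of women on biennial schedules is not given.
- **Low 3-year power as an error.** The article claims power only at 5 years, and low power does not itself raise the false-positive rate. It is a reason not to let the 3-year look decide. Whether λ1, described as based on breast cancer incidence at baseline, suits an advanced-cancer outcome is a separate question.

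**Conclusion.** The point holds as an inconsistency over the decision horizon. The article gives one primary superiority outcome a three-horizon comparison, a whole-follow-up definition, a percentile truncation and a 5-year sample size, and it does not reconcile them.

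If superiority could be claimed at any of 3, 5 or 10 years without adjustment, the one-sided type I error could rise from 5% to as much as about 10%. That figure assumes a constant event rate and no shared adjustment variance. With shared variance of 0.5 to 2 times the 5-year log-IRR variance (assumed), it is about 8 to 9%. The 3-year comparison would have about 61 to 63% power for RR 0.81 at the stated rate. No direction of bias at 3 years is established. The point is worth correcting because the remedy is nearly free and keeps the error rate and power that the article already quotes.

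**What to change.** Name 5-year cumulative incidence of stage II or higher cancer, the horizon that was sized, as the single confirmatory comparison. Label the 3-year result descriptive and the 10-year result a secondary analysis of durability. Add the 5-year horizon to the primary outcome entry in Table 1. State how the 75th-percentile truncation relates to the 5-year comparison, so that it does not set a different horizon. Correct the rationale in Study design so that it matches the 3-, 5- and 10-year schedule.

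This takes a few sentences and no new data. The downside is that neither the 3-year nor the 10-year data could support a confirmatory superiority claim, although both remain reportable with their confidence intervals.

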### Interventional cohort

The prospective interventional cohort consists of women aged 45 years from two provinces in the Veneto Region. The enrollment phase for this cohort has been completed, with a final number of participants of 10,269 women. Participants initially met specific criteria and are now undergoing successive screening rounds with different intervals and imaging protocols until the age of 50.

During the initial screening round, participants underwent two-view digital breast tomosynthesis (DBT) of both breasts. They also completed a questionnaire on risk factors such as personal characteristics, hormonal factors, family history of breast cancer, lifestyle, and health status. Volumetric breast density (VBD) values were calculated with Volpara software from DBT images [45]. Subsequently, women with an average VBD greater than 25% were invited for supplemental ultrasound (US). Based on individual risk factors and mean VBD, we used the Tyrer-Cuzick risk model to estimate lifetime risk (LTR) for each woman [17, 22]. This risk assessment categorized women into five subgroups each recommended for a personalized screening protocol:*Low-Risk, Nondense Breasts*: Women with LTR ≤ 17% and VBD < 25% are recommended for biennial DBT screening;*Low-Risk, Dense Breasts*: Women with LTR ≤ 17% and VBD ≥ 25% are recommended for biennial DBT screening with supplemental US (DBT + US protocol);*Intermediate-Risk, Nondense Breasts*: Women with LTR between 17 and 30%, or LTR > 30% without family history, and VBD < 25% are recommended for annual DBT screening;*Intermediate-Risk, Dense Breasts*: Women with LTR between 17 and 30%, or LTR > 30% without family history, and VBD ≥ 25% are recommended for annual DBT + US screening;*High-Risk, Any Breast Density*: Women with LTR > 30% and a family history of breast cancer, are recommended for annual DBT and magnetic resonance imaging (MRI) surveillance, regardless of breast density.

These individualized recommendations based on density and risk offer personalized screening protocols. For low to intermediate risk nondense breasts, DBT examinations were/are performed during initial and subsequent rounds and interpreted independently by two breast radiologists. For dense breasts at low or intermediate risk, DBT and US are performed by a single breast radiologist. Abnormal findings require further evaluation, including additional imaging and, if necessary, biopsy. Post-treatment follow-up plans are initiated for confirmed breast cancer cases. Informed consent was obtained by all women participating in the interventional cohort.

